### Randomization

Randomization is executed by random drawing of sealed, opaque envelopes. According to the sample size calculation, 50 participants will be allocated to each group, hence 100 identical A5 envelopes have been sealed – each containing a folded note whereupon either “*operative”* or “*conservative”* is written. In order to assure similar timewise enrolment the following measures will be applied (Fig. 2). The 50 envelopes for operative treatment will be packed into stacks of 5 envelopes. The same will be done with the 50 envelopes for conservative treatment. One stack of each treatment arm will be mixed resulting in an equal chance to draw either treatment or intervention among the ten envelopes. The including health care personnel will draw one of the 10 envelopes and hence allocate the participant randomly to either treatment arm 1 or 2. When there are only three envelopes left, one stack of each group will be opened and mixed into the remaining. By this measure, the health care personnel cannot predict the allocated treatment based upon the order of previous mixed treatment allocation from the mixed pool of small envelopes.

**Fig. 2 Fig2:**
[figure not shown]
Illustration of the randomisation process regarding intervention groups, e.g. treatment arm 1 and 2. Each dot represents a sealed, opaque envelope that contains a note with the treatment arm allocation. The blue and red dots represent “conservative” and “operative” treatment, respectively. Whenever only 3 envelopes are left, 5 new “operative” and 5 new “conservative” treatment envelopes are mixed and added

### Interventions

#### Interventions when a possible participant addresses the emergency room

After diagnosing the fracture on a standardized wrist radiograph (anterior-posterior projection and lateral projection) in the emergency room, the physician on call has two attempts to achieve an acceptable closed reduction under local analgesia with a 20 mg/ml Lidocaine hematoma block. While the effect of the hematoma block sets in, nurses measure the arm to be able to lay a proper dorsal plaster cast immobilization. Fluoroscopy is readily available in the emergency room and guides the closed reduction and plaster immobilization. After reduction standardized radiographs are obtained at the department of radiology and the quality of the closed reduction is assessed by the physician on duty. If the radiologic eligibility criteria are fulfilled after closed reduction, the patient is informed about the study and offered enrollment. If the fracture is less severe, e.g. without any of the radiologic criteria warranting closed reduction or operation as mentioned above, the wrist is immobilized with a plaster cast without closed reduction.

#### Intervention group

Treatment arm 1:Open reduction and volar plate fixation utilizing Acu-Loc®, Acumed or Variax®, Stryker with a standard Henry approach to the distal radius and pronator quadratus repair if possible. The vast majority of patients will be operated in regional anesthesia and the remaining patients in general anesthesia. It is the choice of the surgeon whether a tourniquet will be used. After surgery the wrist is immobilized in a dorsal plaster cast for 2 weeks followed by further 3 weeks of immobilization with a removable orthosis. A single hand therapeutic instruction will take place.
Treatment arm 2:Conservative treatment consists of dorsal plaster cast immobilization for 5 weeks. Only discomfort, neurologic deficits or signs of infection warrant removal and replacement with another dorsal plaster cast. A single hand therapeutic instruction will take place.

#### Control group

Patients with less displaced fractures, before or after and eventual closed reduction will be:Conservatively treated as described for treatment arm 2.Patients in the control group that fulfill the radiologic criteria after 2 weeks due to loss of reduction, are offered operative treatment according to the NCG and hence will be excluded from the trial.The investigators reserve the right to exclude a participant if it is considered clinically irresponsible to let them continue.

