**Methods:**

In this single-center, single-blinded randomized-controlled trial, patients ≥65 years with distal radius fractures will be invited to participate. A total of 50 patients per treatment arm is required to provide 80% statistical power at a 5% alpha level assuming a difference of 20% in complication rate between operatively and conservatively treated patients. Primary outcome measures will be complication rate, Quick DASH score (Quick Disabilities of the Arm, Shoulder and Hand), PRWE (Patient rated Wrist evaluation), and range of motion of the wrist. Secondary outcome measures will be grip strength, pinch gauge, pain, use of pain medication EQ5D score (European Quality of life – 5 dimensions), standardized radiographs. One year of follow-up is planned with data collection at the day of injury, after 2 weeks, after 5 weeks, after 6 months, and after 12 months. An intention-totreat and per-protocol analysis will be performed.

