#### Statistical analysis plan

That data will be analyzed using Fisher’s exact test and Mann Whitney U test. The desired applied statistic is odds ratio with Pearson’s 95% confidence interval. Should any data be lost in the follow-up, the Last Observation Carried Forward concept will be used. Treatment arm 3 will be analyzed after 6 months follow-up and published separately.

All test will be two-tailed and assessed at the 5% alpha level. Categorical measures will be presented as percentages. An intention-to treat and per-protocol analysis will be considered. Continuous measures will be presented as means with standard deviations and medians with inter-quartile range. Treatment effects over time will be assessed using linear mixed effect models with patient treated as random factor. A normal distribution with an identity link function will be assumed for continuous measures, while a multinomial distribution and cumulative logit function will be applied to ordinal outcomes.

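### A discretionary exclusion clause of unclear scope, and conflicting statements on intention-to-treat, leave open whether every randomised patient is followed and analysed as allocated

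*Protocol article*

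**What the plan says.** Two exclusion rules stand in the Protocol article, Interventions, Control group.

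- A fixed rule for arm 3. It concerns control patients who come to meet the radiologic criteria at 2 weeks through loss of reduction. They "are offered operative treatment according to the NCG and hence will be excluded from the trial".
- A discretionary rule, which follows directly: "The investigators reserve the right to exclude a participant if it is considered clinically irresponsible to let them continue". It speaks of a participant, not of a control patient. It gives no criterion beyond clinical judgement and does not say what exclusion means for follow-up or for data already collected.

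The article describes the analysis set in two places.

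- Abstract, Methods: "An intention-totreat and per-protocol analysis will be performed".
- Statistical analysis plan section: "An intention-to treat and per-protocol analysis will be considered".

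The same section gives a missing-data rule, "Should any data be lost in the follow-up, the Last Observation Carried Forward concept will be used", which does not mention excluded participants. It also places arm 3 outside the main comparison: "Treatment arm 3 will be analyzed after 6 months follow-up and published separately".

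**The concern.** A decision that treatment should not go on as planned is a clinical matter. Leaving the trial is a separate, statistical one. The discretionary sentence joins the two. If it covers arms 1 and 2, patients could leave the comparison because of how they fared after allocation, and the groups compared would no longer be those that randomisation formed.

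An intention-to-treat analysis of everyone randomised, with follow-up continued, would be the safeguard. The article does not settle that safeguard, because its two statements about it disagree and the weaker one stands in the analysis section.

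The primary outcome is a count of complications in arms of 50, so a handful of patients can change the result. Arm 3 raises a smaller, separate matter: a group that loses its reduction failures by rule cannot describe the course of all minimally displaced fractures treated in a cast.

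**Working it through.** **1. Scope of the two rules**

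| | Fixed rule | Discretionary rule |
|---|---|---|
| Patients named | Control group | Any participant, under the Control group heading |
| Trigger | Loss of reduction at 2 weeks | Investigators' judgement |
| Randomised arms affected | No | Not stated |
| Follow-up and analysis afterwards | Out of the trial | Not stated |

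The randomised arms are therefore exposed only through the second column.

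**2. The plan's own figure**

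The Sample size section asks for at least 49 per group for a 20-point difference, alpha 5%, power 80%. The two rates are not given. Assuming 25% and 5% (mean 15%), pooled variance, two-sided:

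n = [1.96·√(2 × 0.15 × 0.85) + 0.8416·√(0.25 × 0.75 + 0.05 × 0.95)]² / 0.20² = (0.990 + 0.408)² / 0.04 ≈ 48.8, so 49.

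The figure reproduces under that assumption and is not disputed. Against the 50 planned per arm it leaves room for one exclusion per arm.

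**3. Sensitivity of the result to a few exclusions**

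The counts are assumed. The test is the plan's two-sided Fisher's exact test.

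| Excluded, all with complications | Plating | Casting | Difference | p |
|---|---|---|---|---|
| None | 14/50 (28.0%) | 7/50 (14.0%) | 14.0 points | 0.140 |
| Two cast patients | 14/50 (28.0%) | 5/48 (10.4%) | 17.6 points | 0.040 |
| Three cast patients | 14/50 (28.0%) | 4/47 (8.5%) | 19.5 points | 0.018 |
| Three plated patients | 11/47 (23.4%) | 7/50 (14.0%) | 9.4 points | 0.299 |

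For the first row, the two-sided p is the sum of hypergeometric probabilities no larger than that of the observed table, with 21 events among 100 patients: 0.0698 + 0.0698 = 0.140. For the third row, with 18 events among 97: 0.0125 + 0.0057 = 0.018.

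**4. Type I error if exclusion is one-sided**

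Let both arms have the same true complication rate p, with 50 per arm. Let each complicated patient in one arm be excluded with probability q. The number excluded is binomial (50, pq), and the rate among those left is p(1 − q)/(1 − pq). Exact enumeration of Fisher's test at the 5% level gives:

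| p | q = 0 | q = 20% | q = 40% |
|---|---|---|---|
| 14.6% (the team's own plating estimate, Background) | 2.4% | 3.8% | 7.8% |
| 25% (assumed) | 3.0% | 5.7% | 13.5% |

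For example, with p = 25% and q = 40% the rate among those left is 0.15/0.90 = 16.7%. The values of q are assumptions, as the documents give no exclusion rate.

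**The case against.** The strongest case on the other side has five parts.

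- **Intention-to-treat is promised.** The abstract says so, and ranking the analysis sets is something an article may leave to a fuller document. The first part stands: a reader might infer from the analysis section that no intention-to-treat analysis is promised, and the abstract contradicts that. What remains is a conflict within the article, which an unseen document does not remove.
- **The only rule tied to treatment failure is for arm 3.** This stands. Arm 3 is not randomised and is reported separately, and loss of reduction is not on the complication list under Primary outcomes. The rule therefore removes no patient from the plating-versus-cast comparison and, in itself, no primary-outcome event.
- **The discretionary clause may be meant for arm 3 alone.** Its placement allows that reading and its wording allows the wider one. The text does not decide between them.
- **No direction of bias is shown.** A reader might infer that badly faring cast patients would be the ones removed, in favour of the trial's hypothesis. That is plausible: arm 2 patients meet the criteria for surgery, and nothing says that whoever decides on exclusion is blinded. The documents do not establish it. Under Secondary outcomes, week-2 films in the conservative group are not reviewed until follow-up is over, so there is no scheduled radiographic trigger in arm 2. The clause could equally remove a plated patient with a deep infection or hardware failure.
- **Some safeguards exist.** Complications are collected at every visit, a patient's positive answer may not be deleted, and lost data are carried forward. An event recorded before exclusion might therefore survive in the analysis. These rules help, but none names excluded patients, and none captures events after exclusion.

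**Conclusion.** The point holds in a limited form. The article permits exclusion after enrolment on judgement alone, leaves open whether randomised patients are covered and whether they remain in follow-up and analysis, and contradicts itself on intention-to-treat.

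If the clause is used in arms 1 or 2 and excluded patients are dropped, the complication comparison could be biased either way. In the illustration, two or three exclusions of cast patients with complications are enough to cross the 5% threshold. That is a constructed case: it assumes the event counts, exclusions in one arm only (three of seven is 43% of the complicated cast patients), and loss of their recorded events. With 20% one-sided exclusion the type I error stays at 3.8% to 5.7%; at 40% it reaches 7.8% to 13.5%. The size is thus conditional, and the documents do not support predicting that such exclusions will occur.

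For arm 3 the selection is certain, because it follows from the rule, but it limits only the separate arm 3 report.

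**What to change.** 1. State which arms the discretionary clause covers.
2. Distinguish stopping the allocated treatment from leaving follow-up and from leaving the analysis. A randomised patient whose treatment is stopped stays in follow-up and is analysed as allocated, unless consent is withdrawn.
3. Reconcile the abstract and the Statistical analysis plan section: the intention-to-treat analysis of all randomised patients is performed and is primary, with per-protocol as supporting.
4. Report the number of exclusions and the reasons for them, by arm.
5. Keep arm 3 patients who lose reduction in follow-up, and give their proportion as a result in the arm 3 report.

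No clinical decision changes, and no view is taken on when a patient's treatment should be altered. The cost is a few sentences of protocol and analysis wording, and some additional attendances at visits already on the schedule.

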### Outcomes

Summarized in Table 1.

**Table 1 Tab1:** Illustration of timeline and outcome measures including baseline demographics

	DRF	2 weeks	5 weeks	6 months	12 months
Primary outcome complications					
Questionaire	x	x	x	x	x
Examination	x	x	x	x	x
Secondary outcome					
Patient reported outcome					
Quick DASH (DK)	x	x	x	x	x
PRWHE (DK)				x	x
EQ5D				x	x
Pain at rest (0–10)	x	x	x	x	x
Objective examination					
Wrist range of motion			x	x	x
Grip strength				x	x
Pinch gauge				x	x
Wrist radiographs	x	x	x		
Baseline demographics:					
Age, gender, hand dominance, working status, ASA class, diabetes, smoking, alcohol consumption					

Illustration of timeline and outcome measures including baseline demographics Abbreviations: *Quick DASH (DK)* The quick disability of the arm, shoulder and hand outcome measure - validated Danish translation, *PRWHE (DK)* Patient-related wrist evaluation score - validated Danish translation, *ASA class* American Society of Anesthesiologists Classification

#### Primary outcomes

The complication rate will be estimated at day 0, 2 weeks, 5 weeks, 6 months, and 12 months after the injury.

Complications are defined as the presence of:Sensory disturbance, including carpal tunnel syndrome and chronic regional pain syndromeFlexor tendon rupture and irritationExtensor tendon rupture and irritationHardware failure, e.g. osteosynthesis looseningInfection: superficialInfection: deepReoperation with hardware replacementReoperation with hardware removal (partial or total), which is not routinely performed in DenmarkVascular compromised (capillary refill ≥2 s)

Patients will report complications at the given timepoints by answering a questionnaire stating either yes / no and a free-text explanation. If the patient states any complications, a member of the research group will qualify the answer and fill in the free text. However, a YES can only be qualified and shall never be erased if the physician does not agree with the patient’s opinion or explanation.

The Danish version of the Quick Disabilities of the Arm, Shoulder and Hand [22] will be used to assess the level of functionality prior to injury, after 2 weeks, 5 weeks, 6 months, and 12 months. The minimal clinically relevant difference is 16 to 20-point difference in Quick DASH [19–21].

Range of motion is measured by a registered nurse using a goniometer. To ensure the observer is blinded, the patient is instructed not to talk about the treatment. Furthermore, all wrists will be covered by a glove concealing potential scares (Fig. 3). The following data are thus collected in a blinded fashion wrist flexion, extension, pronation, supination, radial deviation, ulnar deviation. The contralateral side will serve as a reference and history of injuries or operations of the contralateral side will be recorded.

**Fig. 3 Fig3:**
[figure not shown]
A demonstration of the blinding of treatment using a glove

#### Secondary outcomes

The patient reported outcome measure Quick DASH will be supported by the following secondary outcome measures:▪ A Danish version of the Patient rated Wrist Evaluation questionnaire (PRWE) will be evaluated after 6 month and 12 months [23].▪ Grip strength of both left and right hand will be estimated as the maximum and average of score of three repetitions of each hand with alternating hands between attempts after 6 months and 12 months using a dynamometer.▪ A pinch gauge where both left and right hand are evaluated (yes/no) if the participant can pinch a sheet of paper. This is collected after 6 months and 12 months by an unblinded physician or research year student.▪ The potential flexion deficit of the 1st finger towards the base of the 5th finger measured as the distance (cm) from the pulp of the 1st finger to the carpometacarpal joint of the 5th finger after 6 and 12 months.▪ The pulp-to-palm distance of the distal 2nd-5th finger and palmar surface of the side treated for DRF after 6 and 12 months.▪ The experienced pain during activity within the preceding 14 days before the injury and at 6- and 12-months follow-up stated on a 0–10 Numeric Rating Scale (NRS).▪ The pain at rest after 2 and 5 weeks given NRS.▪ EQ5D (European Quality of life – 5 Dimensions) after 6 months and 12 months. This is registered by an unblinded physician or research year student [24].▪ The self-reported use of pain medication at day 0, after 2 weeks, 5 weeks, 6 months, and 12 months.▪ The prescribed use of pain medication compared 12 months before with 3 and 12 months after the injury.▪ Standardized radiographs of the injured wrist at day 0 before and after closed reduction (all groups), week 2 (conservative treatment group, not reviewed before completion of the follow-up period), week 5 (all groups).

*The following baseline demographics* will be recorded: gender, age, side of DRF, hand dominance (right-handed, left-handed, ambidextrous), working status, American Society of Anesthesiologists Classification (ASA class 1–6), smoking (cigarettes/day), alcohol consumption (units/week) and diabetes (yes/no).

### Blinding

The study is single blinded, as all measurements will be performed with a glove masking a potential scare. Hence, the observer will be blinded when examining the participant. Furthermore, before each visit the patient is instructed, not to talk about the received treatment with the observer.

During the planning of the study, sham-operations were taken in consideration in order to blind the participants. However, most DRF are operated wide-awake under regional anesthesia only. The research group considered performing a skin incision and writing a manuscript simulating all the noises and communication, that usually take place during an operation. However, the efficacy of this potential blinding of participants during wide-awake surgery was deemed questionable. General anesthesia would have been a viable option, but it would vary too much from the current practice to be feasible at our hospital.

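### The Blinding section claims glove masking for all measurements, but the pinch test and EQ5D are assigned to unblinded staff

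*Protocol article*

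**What the plan says.** The Blinding section of the protocol article rests the single-blind label on the glove, "as all measurements will be performed with a glove masking a potential scare". It then draws the consequence: "Hence, the observer will be blinded when examining the participant". Patients are also told not to discuss their treatment with the observer.

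The Primary outcomes section describes how this works for one outcome. "Range of motion is measured by a registered nurse using a goniometer", and "all wrists will be covered by a glove concealing potential scares". It then lists six wrist movements as the data collected blinded in this way.

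The Secondary outcomes section says of the pinch test: "This is collected after 6 months and 12 months by an unblinded physician or research year student". Of EQ5D, also taken at 6 and 12 months, it says: "This is registered by an unblinded physician or research year student". For grip strength and the two finger-distance measures it names neither a collector nor a masking status.

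On immobilization, the Intervention group section gives arm 1 two weeks of plaster and then "further 3 weeks of immobilization with a removable orthosis", and gives arm 2 five weeks of plaster. Table 1 has range of motion measured at 5 weeks, 6 months and 12 months.

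**The concern.** The Blinding section makes a universal statement, and another section of the same article names exceptions to it. The title and abstract carry the single-blind label, and the only blinding limitation given in the Discussion is the lack of sham surgery. A reader would take every observer-made assessment to be masked.

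What is at stake is assessor bias that could be avoided. The pinch test is a pass/fail judgement made at the bedside, and someone who knows the allocation makes it. At the same two visits a blinded nurse is already examining the same wrist. EQ5D depends less on the assessor, but having unblinded staff register it leaves a route for influence that self-completion would close.

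**Working it through.** There is no figure to reproduce. The check sets the sections of the protocol article side by side.

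**Step 1: the general claim against the named exceptions.** The Blinding section covers all measurements and the observer's examination of the participant. The pinch test is an examination: can the participant pinch a sheet of paper, yes or no. It falls under both statements, yet its collector is unblinded, so the two sections cannot both be true. EQ5D is a questionnaire. It falls under the first statement if a questionnaire counts as a measurement, and it is not naturally an examination. Staff registering it are nevertheless described as unblinded, so the claim does not cover it either.

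**Step 2: the examined outcomes that a glove could mask.**

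| Outcome type | Visits | Collector stated | Masking stated |
|---|---|---|---|
| Wrist motion (six movements) | 5 weeks, 6 and 12 months | Registered nurse | Blinded, with glove and no-talking instruction |
| Pinch test | 6 and 12 months | Physician or student | Unblinded |
| Grip strength | 6 and 12 months | None | Only the general sentence in Blinding |
| Finger distances | 6 and 12 months | None | Only the general sentence in Blinding |

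Of four types, one is explicitly blinded, one explicitly unblinded and two are covered only by the general sentence. The other three types share the 6- and 12-month visits with motion, so the nurse is already present when they are due.

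**Step 3: outcomes outside this count.** Quick DASH, PRWE, pain and self-reported medication come from patients who know their treatment. Radiographs would show a plate. A glove could mask none of these. Complications are reported by the patient and then qualified by a member of the research group. No masking status is given for that step, although a reported yes may not be erased.

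**Step 4: week 5.** Arm 1 has 2 + 3 = 5 weeks of immobilization and arm 2 has 5 weeks, so both periods end at the visit where motion is first measured. The movements listed cannot be measured in plaster, so the device is presumably off and the glove has only a scar to hide. The devices worn until then differ by arm, and the article does not say whether the nurse could see them.

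**The case against.** The strongest reply has four parts.

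- **The exceptions are disclosed.** The article states openly that pinch and EQ5D are collected unblinded, so a careful reader is not misled. This stands in part: the information is there. It still leaves a universal claim in the Blinding section that is untrue as written. Because the article states both sides, the conflict does not come from condensing a fuller protocol.

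- **The stakes are modest.** Pinch and EQ5D are secondary outcomes, pinch is a coarse test, and EQ5D is answered by patients who know their arm. This stands, and it limits the weight of the point.

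- **The stronger readings fail.** A reader might infer that observer blinding fails altogether, or that most outcomes are unblinded. The documents do not support either. Masking of motion is specified and, at 6 and 12 months, uncontradicted. Silence about who measures grip and finger distances does not show that the assessor is unblinded. A count over all outcomes would include patient-reported and radiographic ones that no glove could mask. A reader might also infer that the cast or orthosis defeats the glove at week 5. Nothing says that a device is worn during measurement, and both immobilization periods end then. Who removes the device, and where, is clinic detail that an article commonly leaves to the full protocol.

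- **The glove could disturb finger tests.** Fig. 3 is not shown, so the glove's coverage is unknown. If it covers the finger pulps, it could alter pinch and finger distances. This stands and is a condition on the remedy.

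**Conclusion.** The concern holds in a limited form. The Blinding section's claim is wrong for the pinch test, where the contradiction is direct, and for EQ5D, where it depends on counting a questionnaire as a measurement. It is not contradicted for wrist motion at 6 and 12 months. For grip and finger distances it rests on a general sentence that the pinch test shows to be unreliable.

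In extent, this is one of four glove-maskable examination types plus one questionnaire, each at two visits and both secondary. The document gives no figure from which the size or direction of any bias could be calculated. Week 5 is a matter for precaution and not a stated failure. It deserves a sentence because the abstract and the Primary outcomes section treat motion as primary, although Table 1 lists it as secondary.

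The change is worth making because the statement is wrong as written and the remedy uses staff and visits already planned.

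**What to change.** 1. Have the nurse who measures motion in the gloved wrist also do the pinch test, grip strength and finger distances at the same 6- and 12-month visits, provided the glove leaves the fingers free. If it does not, keep the affected tests as they are and report them as unblinded.
2. Have patients complete EQ5D themselves.
3. Replace the universal sentence in the Blinding section with a list of the outcomes that are observer-blinded. Report any outcome still collected by unblinded staff as unblinded, and state the status of the step that qualifies complications.
4. As a precaution at week 5, take off the cast or orthosis and fit the glove out of the nurse's sight, or report week-5 motion as possibly unblinded.

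The cost is a few more minutes of the same nurse's time and a narrower blinding claim, with no added visits. Step 4 needs someone other than the nurse to remove the device. If nobody is available, the reporting alternative applies.
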